### ^Ethics, registration, funding, conflicts of interests, and result presentation^

The trial is conducted in accordance with the latest versions of the Declaration of Helsinki, Good Epidemiological Practice, and local regulatory requirements, including the German Federal Data Protection Act (Bundesdatenschutzgesetz). The protocol was approved by the ethics committees of Rhineland-Palatinate [837.533.17 (11367)], Baden-Wuerttemberg [B-F-2018-042], and Hessen [MC 84/2018]. The protocol is registered with the German Clinical Trials Register (DRKS00013972). Written informed consent is obtained from all patients before enrolment.

The trial is supported by a grant from the Federal Joint Committee (01NVF16015). None of the authors declare any conflicts of interest. Results will be presented at congresses and published in a peer-reviewed medical journal according to the guidelines of the International Committee of Medical Journal Editors.

### ^Study start and duration^

The 1st patient was recruited in May 2018, the last patient was recruited in March 2020, and follow-up will end in February 2021.

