## Abstract

Background and purpose — Knee and hip replacement are common and increasing procedures, and an optimized care process that could be implemented in different settings would be useful. The PROMISE trial investigates whether a new care process works equally in different German settings and how the results compare with current non-standardized care.

Patients and methods — This multi-center prospective mixed-method study includes 2,000 German patients receiving arthritis-related hip or knee endoprostheses. An interdisciplinary and cross-sectoral care process was developed and implemented in 3 German hospitals with different levels of care, and corresponding rehabilitation centers were included to bridge the gap after acute care.

Duration and outcome — The PROMISE trial recruited patients between May 2018 and March 2020. Follow-up will end in February 2021. Assessments are performed at: examination on clinical indication, 1 week before surgery, on the day of surgery, at the end of hospitalization, end of the rehabilitation program, and 3 months, 6 months, and 12 months after surgery. Outcomes include patient-reported outcomes, medical examination findings, and routinely collected data regarding the surgery and complications. Guideline-based interviews are conducted with selected patients and care partners. The primary endpoint is the presence of chronic pain at 12 months after surgery. Secondary endpoints are the number of recognized pre-existing conditions, physical activity at 12 months after surgery, use of medical services, quality of life, and interactions between care partners.

Trial registration — The trial is registered with the German Clinical Trials Register (https://www.drks.de; DRKS00013972; March 23, 2018).

With demographic changes joint replacement is becoming one of the most frequently performed surgeries. In Germany, approximately 175,000 total hip arthroplasties (THA) (IQTIG 2018a) and 148,000 total knee arthroplasties (TKA) (IQTIG 2018b) are performed each year.

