### ^Endpoints^

#### Primary endpoint

The primary endpoint is presence of chronic pain at 12 months after surgery, evaluated with the pain subscore from the Western Ontario and McMaster Universities Osteoarthritis Index (WOMAC). Approximately 9% of patients report pain at 12 months after surgery (Beswick et al. 2012) and the evaluation is planned using a 2-sided binomial test. The WOMAC is calculated using the hip osteoarthritis outcome score (HOOS) (Klässbo et al. 2003) or the knee osteoarthritis outcome score (KOOS) (Roos et al. 2003).

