### ^Data collection^

Data is collected using an electronic case report form, and the data types, collection processes, and entry processes were jointly developed by the PROMISE group to ensure all participating institutions and functional areas are working to the same standard.

Data is recorded and stored pseudonymized in a central electronic database at a specialized interdisciplinary center. During the trial, the investigators and trial site staff receive system documentation, training, and support for the use of the database. Time-point specific questionnaires and forms are completed by the patient, or the attending physician/physiotherapist, or both.

Data collection points (Table) are:
baseline visit,1 week before surgery,day of surgery,hospital discharge,rehabilitation center discharge,3 months (±2 weeks) after hospital discharge,6 months (±2 weeks) after hospital discharge,12 months (±2 weeks) after hospital discharge,and 12 months (±4 weeks) after hospitalization (clinical follow-up).

Baseline data includes age, sex, comorbidities, initial diagnosis according to International Classification of Diseases (version 10), and socioeconomic data. The other collected data includes:
hip disability (HOOS),knee disability (KOOS),patient health quality (PHQ-4/SSD),quality of life (EQ-5D-5L),social support (Oslo Social Support Scale [OSSS]),personal expectations (Hospital for Special Surgery [HSS] score),rehabilitation success (Staffelstein score),and optimism/pessimism (Life Orientation Test-Revised [LOT-R]).

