### ^Estimated sample size and power^

The estimated sample size is based on the primary endpoint (chronic pain at 12 months), which will be evaluated using a 2-sided binomial test. A previous report has indicated that approximately 9% of patients report chronic pain after 1 year (Beswick et al. 2012). Thus, 1,900 patients are required to detect a 20% reduction (i.e., from 9% to 7.2%) based on an α level of 5% and power of 80%. Assuming 5% of patients will be lost to follow-up, the target sample size is 2,000 participants. This sample size also provides power of > 80% for analyzing the 2 confirmatory secondary endpoints (number of anemia cases and physical activity after 1 year; values selected from the literature), which will be analyzed only if a significant improvement is observed in the primary endpoint.

The secondary analyses are based on non-inferiority tests and previously reported values. The number of anemia cases will be tested to determine whether it is ≤ 2% below the expected reference value of 15.5% for Central Europe (McLean et al. 2009). Physical activity will be tested using the HOOS-PS/KOOS-PS to determine whether the patients achieve at least the minimum clinically important improvement (23 points) (Paulsen et al. 2014). To comply with the α-error, confirmatory testing for these 2 secondary endpoints will be performed only if statistically significant improvement is observed for the primary endpoint. To evaluate the achievement of a plateau in the number of interactions between care partners, the implementation period is divided into 3 intervals. The number of interactions in intervals II and III will be tested for equality. The criterion for equality will be based on the difference between the 1st and 2nd intervals. Poisson models will be used to compare the numbers of healthcare interactions between PROMISE participants and the control group, with sub-analyses according to different cost categories (e.g., hospital stays vs. general practitioner visits). Factors that potentially influence healthcare utilization, interactions, and quality of life will be evaluated using hierarchical regression models with care partners considered as clusters.

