
**Table ut0001:** Data collection, time-points, and instruments

Item/score	A	B	C	D	E	F	G
Basic information	X						
Comorbidities **^a^**	X						
Staffelstein	X			X	X		X
Indication	X						
ASA		X					
Preop. anemia assessment		X					
HOOS/KOOS ^a^	X					X	
EQ-5D 5L ^a^	X			X	X	X	
PHQ-4/SSD ^a^	X	X		X	X	X	
OSSS, LOT-R ^a^	X						
HSS or INDICATE knee (preop) ^a^	X						
HSS or INDICATE knee (postop) ^a^						X	
ISAR ^a^		X					
Timed up & go and VAS/NRS		X		X	X		X
Socioeconomic data ^a^	X					X ^b^	
Cost book ^a^				X		X	
Functional goal ^a^						X	
Surgery			X				
Implant details			X				
Functional milestones and discharge				X			
Complications				X			
Rehabilitation					X		
Thrombosis/							
bleeding				X	X		
Follow-up ^a^						X ^b^	
Clinical follow-up							X

A.Indication, 8 weeks preoperatively

B. Preoperative assessment, 1 week preoperatively

C. Operation

D. Hospital stay

E. End of rehabilitation

F. Follow-up at 3, 6, and 12 months postoperatively

G. Clinical follow-up at 12 months postoperatively

**^a^**Patient-reported outcome.

**^b^**Only at the 12-month follow-up

ASA: American Society of Anesthesiologists score,

HOOS: Hip disability and Osteoarthritis Outcome Score,

KOOS: Knee injury and Osteoarthritis Outcome Score,

EQ-5D 5L: EuroQol Group 5-level EQ-5D version,

PHQ-4: Patient Health Questionnaire-4,

SSD: somatic symptom disorders,

OSSS: Online Social Support Scale,

LOT-R: Life Orientation Test-Revised,

HSS: Hospital for Special Surgery,

ISAR: International Society of Arthroplasty Registries,

VAS: visual analogue scale,

NRS: numerical rating scale.

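### The stated calendar (last recruitment March 2020, follow-up closed February 2021) fits a 12-month primary endpoint only under a narrow reading of 'recruited', and the sample size has no slack for the difference

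*Protocol article*

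**What the plan says.** All references are to the protocol article.

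- **Calendar.** Study start and duration states that "the last patient was recruited in March 2020, and follow-up will end in February 2021". The Abstract gives the same dates: "The PROMISE trial recruited patients between May 2018 and March 2020. Follow-up will end in February 2021". The two places agree, so this is not a slip in one of them.
- **Endpoint.** Primary endpoint: "The primary endpoint is presence of chronic pain at 12 months after surgery". It is scored with the WOMAC pain subscore, derived from HOOS or KOOS.
- **When the questionnaire is due.** The Table of data collection marks HOOS/KOOS after surgery only in column F, "F. Follow-up at 3, 6, and 12 months postoperatively". Data collection times that questionnaire at "12 months (±2 weeks) after hospital discharge". The wider window, "12 months (±4 weeks) after hospitalization (clinical follow-up", belongs to the clinical visit (column G), where HOOS/KOOS is not marked.
- **When patients enter.** Study subjects and eligibility criteria ties enrolment to meeting the criteria for surgery. The Table places the visit at which the indication is made, with baseline HOOS/KOOS, at "A.Indication, 8 weeks preoperatively". The article does not say whether 'recruited' means enrolled at that visit or operated.
- **Allowance for loss.** Estimated sample size and power requires 1,900 patients and continues: "Assuming 5% of patients will be lost to follow-up, the target sample size is 2,000 participants". Patient withdrawal adds that withdrawn patients are not replaced.

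**The concern.** From some day in March 2020 to some day in February 2021 is about 10 to just under 12 months. The primary endpoint needs 12 months from surgery, and the questionnaire that carries it is timed from discharge, which is later still. If patients counted as recruited in March 2020 were still waiting for surgery, the gap widens by the length of the wait.

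At stake is whether the last patients have a primary endpoint at all by the stated closing date. The primary test is a single-group comparison with a fixed 9% rate, and the two confirmatory secondary tests proceed only if it is significant. The size calculation allows for 5% ordinary loss and nothing for a calendar cut-off.

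**Working it through.** **1. The plan's own figure.** Inputs from Estimated sample size and power: p0 = 0.09, p1 = 0.072, two-sided α = 0.05, power 80%, one-sample binomial test.

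Normal approximation: n = [(1.960·√(0.09·0.91) + 0.842·√(0.072·0.928)) / 0.018]² ≈ 1,871; with continuity correction, 1,926. The exact equal-tailed test at n = 1,900 has power 80.6%. The stated 1,900 is reproduced.

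Loss allowance: 1,900 / 0.95 = 2,000, with no remainder. Any further loss leaves fewer than 1,900.

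**2. The gap in days.** Take the closing date most favourable to the plan, 28 February 2021. From 1 March 2020 that is 364 days; from 31 March 2020 it is 334 days.

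With the 8-week lead, a patient recruited on 31 March 2020 is operated on around 26 May 2020. That is 278 days (about 9 months) before closure. The earliest in-window questionnaire, even with no hospital stay, is 26 May 2021 − 14 days = 12 May 2021.

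**3. Latest usable recruitment date.**

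Cut-off = 28 Feb 2021 − (365 − w + s + L) days, where:

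- w = early edge of the window used (0 or 14 days; Data collection)
- s = hospital stay (0 or 10 days; 10 is the German median in the Discussion, used here as an upper assumption)
- L = lead from recruitment to surgery (0, or 56 days from the Table)

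**4. Share cut off.** Assumption: uniform accrual of 2,000 patients from 1 May 2018. The last recruitment is on 1 March 2020 (670 days) or 31 March 2020 (700 days). Share = (last recruitment − cut-off) / accrual days, not below 0. Evaluable = 0.95 × 2,000 × (1 − share).

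Worked case: L = 56, s = 10, w = 14, last recruit 31 March. 365 − 14 + 10 + 56 = 417 days, so the cut-off is 8 January 2020. Share = 83/700 = 11.9% (237 patients). Evaluable = 0.95 × 1,763 = 1,675.

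With the ±2-week window applied (w = 14):

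| Lead L | Last recruit | Stay s | Cut-off | Cut off | Evaluable | Exact power |
|---|---|---|---|---|---|---|
| 0 | 1 Mar | 0 | 14 Mar 2020 | 0% | 1,900 | 80.6% |
| 0 | 1 Mar | 10 | 4 Mar 2020 | 0% | 1,900 | 80.6% |
| 0 | 31 Mar | 0 | 14 Mar 2020 | 2.4% | 1,854 | 79% |
| 0 | 31 Mar | 10 | 4 Mar 2020 | 3.9% | 1,827 | 79% |
| 56 | 1 Mar | 0 | 18 Jan 2020 | 6.4% | 1,778 | 78% |
| 56 | 1 Mar | 10 | 8 Jan 2020 | 7.9% | 1,750 | 76% |
| 56 | 31 Mar | 0 | 18 Jan 2020 | 10.4% | 1,702 | 75% |
| 56 | 31 Mar | 10 | 8 Jan 2020 | 11.9% | 1,675 | 75% |

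At nominal 12 months (w = 0) the ranges are 0.1–5.9% for L = 0 and 8.5–13.9% for L = 56. The last case leaves 1,637 evaluable and exact power of 74%.

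**5. Sensitivity.** Starting accrual on 31 May 2018 instead of 1 May moves the tops of the windowed ranges only to 4.0% and 12.4%. Exact binomial power is saw-toothed in n, so differences of a point between neighbouring rows carry no meaning. The smooth approximation runs from 80.7% at 1,900 to 79.0% at 1,827 and 75.2% at 1,675.

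**The case against.** The case on the other side has real substance.

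- **The dates are months, not days.** If 'recruited' means operated, the last operation was between 1 March and about 4–14 March 2020 (depending on stay), and late questionnaires came at the early edge of the window, nobody is cut off. This stands. A reader might infer from the dates that the endpoint certainly cannot be observed in the last recruits and that 1,900 is certainly missed. The article does not support that unconditionally.
- **The larger percentages rest on an inference.** The eligibility section says who is enrolled, not on what date a patient counts as recruited, and 8 weeks is a nominal label. This stands as a limit on the size. The inference is still reasonable, because baseline HOOS/KOOS is collected at the indication visit.
- **The power loss is modest.** True in both readings. With the window applied and recruitment equal to surgery, the calendar cut-off alone never exceeds 5%; only the total loss does.
- **Bias from early assessment.** A reader might infer that late patients would be assessed at 9 to 11 months, counted as 12-month results, and so bias the comparison with the 9% reference. Nothing says that early questionnaires would be counted this way, and no figure shows pain changing between 9 and 12 months. That reading should not be drawn.
- **Handling may be in the analysis plan.** A rule for late questionnaires may well be there, and its absence from an article is no fault. But the article does state specific dates and a specific endpoint time, and these need to agree.
- **Surgery versus discharge as anchor.** The difference is the hospital stay, which even at 10 days is shorter than the 2-week window. It is a wording matter.

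**Conclusion.** The point holds in conditional form. The stated end of follow-up is incompatible with a 12-month endpoint for the last recruits unless three things are true together: recruitment means surgery, the last surgery was in the first half of March 2020, and late questionnaires fall at the early edge of the window. The ±4-week window does not help, because it belongs to a visit without HOOS/KOOS.

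The size depends on what 'recruited' means. With the window applied, about 0–4% are cut off if it means surgery and about 6–12% if it means the indication visit. At nominal 12 months the ranges are about 0–6% and 8–14%. Exact power is about 79–80% and 74–78% respectively, against 80.6% at 1,900.

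These figures rest on uniform accrual, exactly 2,000 patients, closure on 28 February 2021, a stay of 0 to 10 days, and 5% ordinary loss among the remainder. The date conflict itself does not depend on the accrual or loss assumptions. Nor does the absence of slack: 1,900 is exactly 95% of 2,000.

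**What to change.** 1. Set the end of follow-up to the last surgery (or last discharge) plus 12 months plus the visit window. If the last recruit was operated on 31 March 2020, that is 14 April 2021 counted from surgery, or 24 April with a 10-day stay. If recruitment preceded surgery by 8 weeks, it is 9 June 2021 from surgery, or 19 June with a 10-day stay. The clinical visit, with its 4-week window, would run two weeks later in each case.
2. State whether 'recruited' means enrolment or surgery, and give the date of the last surgery.
3. If the closing date cannot move, limit the primary analysis to patients whose surgery date allows an in-window 12-month assessment, and restate the evaluable number and the power.
4. As a minor wording correction, use one anchor, surgery or discharge, throughout.

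Cost: if February 2021 is simply misstated, a corrected sentence in two places. Otherwise, either a few more months of a questionnaire and clinic visit already in use, or a power statement a few points lower.

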## ^Discussion^

Evidence-based optimized perioperative processes have already been described for hip and knee replacements (Ibrahim et al. 2013, Sprowson et al. 2013). These programs can reduce the length of stay to 1–3 days (Kehlet 2013, Khan et al. 2014) without an increased risk of complications or readmission (Glassou et al. 2014), and have also reduced the 2-year mortality rate from 3.8% to 2.7% (Savaridas et al. 2013). However, most studies regarding process optimization for hip and knee replacement were performed in Scandinavia, the UK, and North America, which complicates generalizations to other countries with different healthcare systems. For example, Germany has more hospital beds per capita that Denmark (8 vs. 2.6 beds/1,000 population) (OECD 2017), the hospital reimbursement system is based on diagnosis-related groups, and insured individuals have a legal right to complete a rehabilitation program. Moreover, the median length of stay is 10 days in Germany (IQTIG 2018a, 2018b), versus only 2 days in Denmark (Husted et al. 2016, Knaealloplastikregister 2017). Thus, the setting in Germany can vary considerably from the setting in previous studies that examined optimized care processes, and we are not aware of any similar studies that were performed in Germany. The PROMISE trial is also designed to account for the fact that German patients participate in a rehabilitation program after their hospitalization. Therefore, we hope this prospective multi-center trial will help improve outcomes in the post-hospitalization period by incorporating hospitals that provide different levels of care as well as outpatient and inpatient rehabilitation centers. The resulting information may guide the development of an optimized process that accounts for the patient’s characteristics, expectations, and quality of life, as well as the relevant stress factors, functional outcomes, and economic costs up to 1 year after surgery. The strengths of the study we see in a prospective, multi-centric, intersectoral design, a relatively high number of participants, a very broad data collection at numerous points of time, an above-average follow-up period and an independent external evaluation. Unfortunately, it is not feasible to organize an optimized and a common treatment path at a single center, which intends randomization of the participants to an intervention and control group. We will at least partially address this issue by comparing the results with those from a matched cohort of control patients from a German health insurance database. Parameters that we cannot directly compare between the PROMISE and control groups will be evaluated based on previously published results. Also disadvantageous is that German funding agencies select the rehabilitation facility and we cannot ensure that all participants complete their rehabilitation in PROMISE-affiliated facilities. Although this may reduce the number of participants who complete the full PROMISE process, it will allow us to analyze statistically the benefits of cross-sectoral care.

**Table ut0001:** Data collection, time-points, and instruments

Item/score	A	B	C	D	E	F	G
Basic information	X						
Comorbidities **^a^**	X						
Staffelstein	X			X	X		X
Indication	X						
ASA		X					
Preop. anemia assessment		X					
HOOS/KOOS ^a^	X					X	
EQ-5D 5L ^a^	X			X	X	X	
PHQ-4/SSD ^a^	X	X		X	X	X	
OSSS, LOT-R ^a^	X						
HSS or INDICATE knee (preop) ^a^	X						
HSS or INDICATE knee (postop) ^a^						X	
ISAR ^a^		X					
Timed up & go and VAS/NRS		X		X	X		X
Socioeconomic data ^a^	X					X ^b^	
Cost book ^a^				X		X	
Functional goal ^a^						X	
Surgery			X				
Implant details			X				
Functional milestones and discharge				X			
Complications				X			
Rehabilitation					X		
Thrombosis/							
bleeding				X	X		
Follow-up ^a^						X ^b^	
Clinical follow-up							X

A.Indication, 8 weeks preoperatively

B. Preoperative assessment, 1 week preoperatively

C. Operation

D. Hospital stay

E. End of rehabilitation

F. Follow-up at 3, 6, and 12 months postoperatively

G. Clinical follow-up at 12 months postoperatively

**^a^**Patient-reported outcome.

**^b^**Only at the 12-month follow-up

ASA: American Society of Anesthesiologists score,

HOOS: Hip disability and Osteoarthritis Outcome Score,

KOOS: Knee injury and Osteoarthritis Outcome Score,

EQ-5D 5L: EuroQol Group 5-level EQ-5D version,

PHQ-4: Patient Health Questionnaire-4,

SSD: somatic symptom disorders,

OSSS: Online Social Support Scale,

LOT-R: Life Orientation Test-Revised,

HSS: Hospital for Special Surgery,

ISAR: International Society of Arthroplasty Registries,

VAS: visual analogue scale,

NRS: numerical rating scale.
